### 2.8. Sample Size

The sample size will be based on the primary outcome of the Falls Efficacy Scale International (FES-I) as a primary outcome measure to determine the effect of the VCI approach. It will be calculated using the G*Power 3.1 program. The a posteriori sample calculation will consider a statistical power of 80% and a significance level of 5% to obtain a clinically relevant change between groups with more than 2.9 change points [38]. The calculation will also assume that 20% of participants drop out of intervention studies.

### 2.9. Statistical Method

Data will be collected and added to a database in Excel XP 2010 Microsoft ^®^ as it is collected. In parallel, the collected data will be stored and analyzed electronically using the Statistics Package for the Social Sciences (SPSS) program, version 20.00 for Windows (SPSS Inc, Chicago, IL, USA), a significance level of 95% will be adopted (*p* < 0.05) for all analyses.

Initially, a descriptive analysis of the variables will be performed using frequencies for categorical variables and mean and standard deviation for continuous variables, to characterize the sample and other analyses. Then, the verification of the normality of the data will be carried out. The behavior of quantitative variables will be performed using mean and confidence interval and if the distribution is not normal, the median and interquartile interval will be considered. Qualitative variables will be analyzed through measures of absolute and relative frequencies. Analyses will follow the intention-to-treat principle.

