#### 2.7.1. Primary Results

Assessment of the risk of falls was performed using the Falls Efficacy Scale International (FES I), an instrument validated for the Brazilian elderly [35]. The internal consistency of the FES-I Brazil was α = 0.93, and the reliability was ICC = 0.84 and 0.91 (intra- and inter-examiners, respectively). A 16-item questionnaire will be answered on a four-point Likert scale (1 = not at all worried, 2 = a little worried, 3 = very worried 4 = extremely worried), totaling 16 items scored on a four-point scale (1 = not at all worried 4 = very worried) [36,37]. This should be reliable to assess fear of falling in older women at higher risk of falling and that the FES I score should change by >3 points or 11% to identify clinical change over time at the group level and the individual level, the sum of the score would have to change by >8 points or 29% [38].

Quality of life will be measured using the WHOQOL-OLD, validated for Portuguese. It comprises 24 items recorded on a five-point Likert scale, divided into six facets: “sensory functioning”, “autonomy”, “past, present, and future activities”, “social participation”, “death and dying”, and “intimacy”. The instrument’s overall score determines that higher scores represent better quality of life in the facets. The instrument has satisfactory characteristics of internal consistency (Cronbach’s coefficients from 0.71 to 0.88), discriminant validity (*p* < 0.01), concurrent validity (Correlation coefficients between −0.61 and −0.50), test–retest reliability (Correlation coefficients between 0.58 to 0.82), usefulness, and good psychometric performance [39,40]. The minimal clinically important differences for quality-of-life measures are variable depending on the method applied and the clinical context of the study [41].

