Adherence will be calculated by the percentage of sessions completed out of the total number of prescribed intervention days (24 sessions = 100%), reported by the researcher. Adverse effects will be counted from the researcher’s record.

After the initial assessment, baseline (t0), there will be three moments for reassessment: after the 8th session (t1), 16th session (t2), and 24th session (t3).

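### The protocol is inconsistent on one or two primary outcomes, names no deciding visit and allows p < 0.05 for every analysis, so the primary claim is not held at 5% if either outcome or any visit can carry it

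*Protocol article*

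**What the plan says.** Four parts of the protocol article bear on this.

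- **Section 2.7.1 (Primary Results)** lists two instruments. One is FES-I: "Assessment of the risk of falls was performed using the Falls Efficacy Scale International (FES I"). The other is WHOQOL-OLD: "Quality of life will be measured using the WHOQOL-OLD, validated for Portuguese".
- **Section 2.8 (Sample Size)** uses only the first: "The sample size will be based on the primary outcome of the Falls Efficacy Scale International (FES-I) as a primary outcome measure". The target is "a statistical power of 80% and a significance level of 5% to obtain a clinically relevant change between groups with more than 2.9 change points". No time point is attached to that change.
- **Section 2.7.2 and Table 3** set the schedule: "there will be three moments for reassessment: after the 8th session (t1), 16th session (t2), and 24th session (t3"). Table 3 marks both FES-I and WHOQOL-OLD at all three. Neither place says which visit decides the trial.
- **Section 2.9 (Statistical Method)** sets the error rule: "a significance level of 95% will be adopted (*p* < 0.05) for all analyses". The 95% is a slip for 5%, as the p-value beside it shows. The section covers descriptive summaries, a normality check and intention-to-treat. It names no between-group test, no order of testing, and no rule on whether one or both outcomes must succeed.

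**The concern.** A 5% significance level protects the primary claim only if it is clear which comparison makes that claim. Here section 2.7.1 allows two outcomes, section 2.8 speaks of one, the schedule offers three visits, and section 2.9 gives every analysis the full 5%. If the claim may rest on whichever outcome or visit turns out significant, the chance of at least one false positive exceeds 5%, and the headline result can be chosen after the data are seen. Having a blinded researcher run the analysis (section 2.5) does not prevent that choice. The conclusions expect the results to bear on clinical practice and health policy, so the status of the primary claim matters.

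**Working it through.** The document gives no familywise error rate, so there is no stated figure to reproduce. The check asks what the blanket 5% rule implies under each reading that the text permits.

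**Inputs from the document**
- Alpha per analysis: 0.05 (sections 2.8 and 2.9). Sidedness is not stated; two-sided is assumed.
- Groups: 2 (section 2.4), so there is one between-group contrast per outcome and visit.
- Outcomes listed as primary: 2 (section 2.7.1), or 1 (section 2.8).
- Post-baseline assessments: 3 (section 2.7.2, Table 3).

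**Inputs assumed**
- Correlation between visits from 0 to 0.9 and between outcomes from 0 to 0.7. The document gives neither.

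**Independent tests.** The chance of at least one false positive among k tests is 1 − 0.95^k.
- k = 1 (one outcome, one visit): 5%
- k = 2 (two outcomes, each tested once): 1 − 0.95² = 9.75%
- k = 3 (FES-I at three visits): 1 − 0.95³ = 14.3%
- k = 6 (two outcomes at three visits): 1 − 0.95⁶ = 26.5%

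**Correlated tests.** Normal test statistics were simulated with no true effect (1,000,000 draws, rejecting when |Z| > 1.96). The correlation was equal between all pairs of visits and was crossed with the correlation between outcomes.

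Two outcomes, each tested once:
- outcome correlation 0.5: about 9.1%
- outcome correlation 0.7: about 8.4%

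FES-I alone, tested at three visits:
- visit correlation 0.5: about 12.5%
- visit correlation 0.8: 9.9%
- visit correlation 0.9: about 8.4%

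Two outcomes at three visits, any win counting:

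| Visit correlation | Outcome correlation | At least one false positive |
|---|---|---|
| 0.5 | 0 | 23.6% |
| 0.5 | 0.5 | 22.0% |
| 0.7 | 0.5 | 19.2% |
| 0.8 | 0.5 | 17.4% |
| 0.8 | 0.7 | 15.9% |
| 0.9 | 0.5 | 14.8% |
| 0.9 | 0.7 | 13.7% |

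The six-test range is therefore about 14% to 26%. Counting only false claims in favour of vibration, the same six tests give about 7-14%, to be compared with 2.5% for a single two-sided 5% test.

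**Both outcomes required at one fixed visit.** The chance that both are falsely significant cannot exceed the chance for either alone, so the error stays at or below 5%.

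**After a repair**
- One outcome at one visit: 5%.
- Fixed sequence, FES-I then WHOQOL-OLD, both at t3: at most 5%, because the second test is reached only through the first.
- Alpha split, 0.025 each at t3: 1 − 0.975² = 4.94% if independent.

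**The case against.** The strongest reply is that a journal article condenses a fuller plan, and that the deciding visit, the order of testing and the multiplicity method commonly sit in an analysis plan that is not shown. That holds for technical detail. It does not cover the conflict between sections 2.7.1 and 2.8 on the number of primary outcomes. Nor does it cover the affirmative rule in section 2.9, which a later plan that adjusted alpha would contradict as written.

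A second reply concerns size, and it stands. A reader might infer that the plan carries a false-positive risk of 17-26% as a matter of fact. The document does not support that. The figure needs six separate two-sided tests, a rule that any one win is enough, and a visit correlation no higher than about 0.8. Section 2.9 names no between-group test, so one repeated-measures test per outcome fits the text equally well and gives about 8-10%. Taking section 2.8 at its word, with FES-I as the only primary outcome, gives 5% at one visit.

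Third, the Discussion anticipates benefit on fall risk and quality of life together. If both had to succeed at one visit, the error would not be inflated. The wording states an expectation, however, and not a success rule.

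Two further inferences should be resisted. The six WHOQOL-OLD facets do not add to the count, because no section plans tests on them and section 2.7.1 refers to an overall score. Sizing on one outcome is ordinary practice, so the absence of a power statement for WHOQOL-OLD is not an error in itself.

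**Conclusion.** The point holds in conditional form. The protocol is inconsistent on whether there are one or two primary outcomes, fixes no deciding visit, and applies an error rule that does not keep the primary claim at 5% whenever either outcome or any visit may carry it.

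The size depends on a reading that the document leaves open:
- about 8-10% if either outcome, tested once, may carry the claim;
- about 8-14% for FES-I alone tested separately at three visits;
- about 14-26% for both outcomes tested separately at all three visits with any win counting.

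All three ranges are two-sided and rest on the assumed correlations. The last also rests on a testing scheme that the document does not describe. The defect concerns the trial's main claim and cannot be credibly repaired once the outcome data have been seen, so it should be settled before then.

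**What to change.** Reconcile section 2.7.1 with section 2.8, and replace the blanket rule in section 2.9 with a paragraph such as:

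> The single primary endpoint is the between-group difference in FES-I at t3, tested at a two-sided 5% level. WHOQOL-OLD overall score at t3 is tested at 5% only if FES-I is significant. Results at t1 and t2 and all other outcomes are reported as estimates with 95% confidence intervals and are not confirmatory.

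This agrees with the outcome already used for sizing and with the end of the 24-session programme, and it restores the 5% level. If the sponsor wants both scales to be able to support a claim independently, 0.025 for each at t3 is an acceptable alternative. Correct the 95% significance level to 5% in the same edit.

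The cost is one paragraph, with no extra participants and no change of procedure. Under the fixed sequence, WHOQOL-OLD can support a confirmatory claim only after FES-I succeeds. Under the split, FES-I is tested at 0.025, and the sample-size calculation in section 2.8 would have to use that level.

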## 3. Discussion

To determine the efficacy of WBV combined with MCT in women with osteoporosis and a previous history of falls, an intervention study will be conducted. It is assumed that adding vibration to MCT will decrease the risk of falling and improve the quality of life of the participants.

Models of care for OST include fractures, assessments, education, and exercise programs [10]. Bone health is essential for the elderly and concerning OST, recent evidence indicates that exercise can delay its onset and reduce the risk of falling [26].

A meta-analysis of patients with OST (RR 0.832; CI 0.762–0.909; n: 3569 participants; 10 randomized clinical trials; I2 = 13.4%) observed the effects of exercise in fall-related injuries, thus demonstrating that participants at high risk of falls or with OST would benefit primarily from exercise intervention [8].

Different pieces of evidence bring the importance of exercises and WBV. However, to date, there are few studies with WBV programs added to multicomponent exercises, aimed at improving the risk of falls and the quality of life of women with OST, among these, a randomized clinical trial [58] (n:42 elderly) of a vibration protocol added to exercise on the risk of falls and quality of life observed improvements in balance, gait, and quality of life in the participants undergoing the intervention. In turn [59] in a randomized clinical trial (n:77 elderly) of WBV added to the strength and balance exercises found that the improvement in functional mobility of this WBV addition was greater than in the group that performed the exercise alone.

The MCT refers to the combination of three or more training modalities that involve exercises that involve muscular endurance, aerobic, balance, and flexibility exercises in the same training session [30,60,61]. Given the above, a multicomponent exercise program is recommended to improve physical fitness and reduce the incidence and risk of falls in the elderly [62].

According to authors [63], a meta-analysis of randomized clinical trials found that MCT improves strength and functional performance in the elderly, proving to be a good training strategy for the elderly. In ECR, [64] also verified the improvement of muscular endurance, agility, and dynamic balance in the elderly. A positive effect was demonstrated [61] of CMD and positive health outcomes for the elderly, such as cardiorespiratory fitness, functional skills (muscle strength, balance and gait skills, flexibility, and exercise capacity), in addition, to contribute to reducing the risk of falling and in some aspects of the quality of life of the elderly.

The WBV in patients with OST presents results of increased muscle strength and increased neuromuscular coordination, which can reduce the risk of falls that are often the result of fracture [65], also corroborate the positive findings of clinical trials of WBV in the elderly in improving balance [66], in improving mobility and gait performance [67] in improving different muscle strength proxies, as symmetrical maximum voluntary contraction, dynamic strength, rate of development, and isometric strength of knee extensors [68,69].

It is common knowledge that the high costs and demands of services necessary to manage patients with a history of falls and other complications arising from such a process are common. In addition to this issue, it is known that OST, when left untreated, can bring functional changes in this elderly population. This protocol aims to provide participants and the community in general with skills that provide active and healthy aging, seeking to ensure greater autonomy and independence for this population. So, it is expected that, through this protocol, benefits are possible to alleviate restrictions and promote a more active and functional life.

### Limitations

Some limitations of this protocol should be considered, which may influence the interpretation of the study’s findings, such as patient adherence to the 24-week protocol and the absence of a control group in the study—which does not perform any type of therapy, due to lack this profile of participants since the current guidelines for patients with osteoporosis include the practice of physical activities.

## 4. Conclusions

The development of that protocol based on the addition of whole-body vibration to multi-component training seeks to reduce the risk of falls and improve the quality of life of elderly women with osteoporosis and a history of falls, also hoping to ensure improvements in balance activities, strength, and functional performance, ensuring the safety and social interaction of participating patients. It is essential to infer that the results will have important implications for prevention, non-pharmacological treatment, clinical practice, and health policies, as well as that the elaboration of a detailed and targeted prescription for this target audience, allows its use in current clinical practices or future.

## Figures and Tables

**Figure 1 biology-11-00266-f001:**
[figure not shown]
Consolidated Standards of Reporting Trials flow diagram.

**Figure 2 biology-11-00266-f002:**
[figure not shown]
Participant position during vibration platform.

**Table 1 biology-11-00266-t001:** Multicomponent training protocol model.

Training Session	Exercise	Prescription
Aerobic/cardiorespiratory resistance	Free Walk (1st week)	10 min with an increment of 3–4 CR10 or Borg/per session
	Increase Treadmill walk (2nd–8th week)	
Resistance	Shoulder lift	**Load intensity—1RM**
	Shoulder abduction	1st and 2nd week with slight intensity (40% RM)
	Shoulder girdle dissociation	3rd and 4th week with slight intensity (50% RM)
	Abdominal exercise	5th and 6th week with moderate intensity (60% RM)
	Straight leg lift	7th and 8th week with strong intensity (70% RM)
	Hip adduction	**Frequency**
	Hip abduction	1st week: 1 set of 10 repetitions
	Knee extension	2nd and 3rd week: 2 sets of 10 repetitions
	Ankle plantar flexion and ankle dorsiflexion	4th and 5th week: 2 sets of 12 repetitions
	Sit and get up	6th to 8th week: 2 sets of 15 repetitions
Balance	Orthostasis with bilateral support	1st and 2nd week: bi support tpt/EO/stable
	Orthostasis with unilateral support	3rd and 4th week: uni support tpt/EO/stable
	Tandem posture	5th week: uni support tpt/EO/unstable
	Tandem march and tiptoe	6th week: uni support tpt/EC/stable
		7th week: uni support tpt/EC/unstable
		8th week: without tpt/EC/unstable
		Progressive postures according to the patient, in time of 10–20 s
	Stretching: sternocleidomastoid, scalene, pectoral muscle, quadriceps, and sural triceps	The intensity with a stretch to the point of muscle strain or mild discomfort. Frequency of 2 × 30 s
Fonte: [name], 2020		

Legend: mr: maximum repetition; uni: unilateral; bi: bilateral; tpt: therapist; eo: eyes open; ec: eyes closed.

**Table 2 biology-11-00266-t002:** Protocol of the vibratory platform model.

Session	Session per Week	Time Vibration (s)/Series	Vibration Frequency (Hz)	Amplitude (mm)	Recovery (s)	Total Time of Intervention (s)
1st	3	60/4	12,6	4	10	180
2nd	3	60/4	12,6	4	10	180
3rd	3	60/4	20	4	10	180
4th	3	60/4	20	4	10	180
5th	3	60/4	26	4	20	180
6th	3	60/4	26	4	20	180
7th	3	60/4	30	4	30	180
8th	3	60/4	30	4	30	180

Legend: mm (millimeter); s (seconds); Hz (hertz).

**Table 3 biology-11-00266-t003:** Schematic diagram of timeline of enrollment, intervention, and assessments. Adapted from SPIRIT Group 2013.

	Study period					
	Recruitment	Allocation	Post- allocation			Study finalization
Time point	–t1	0	(t1) 8th session	(t2) 16 th session	(t3) 24 th session	
**Enrolment**						
Eligibility screen	x					
Informed consent	x					
Allocation		x				
**Interventions**						
GTMV						
GTM						
**Assessments**						
FES-I	x		x	x	x	
WHOQOL-OLD	x		x	x	x	
FRT	x		x	x	x	
FRt (BBS)	x		x	x	x	
IRM	x		x	x	x	
DTC6	x		x	x	x	
PGIC					x	
Adhrence			x	x	x	
Adverse effects			x	x	x	

Legend: after the 8th session (t1), 16th session (t2), and 24th session (t3).

## Data Availability

The datasets that will be used and/or analyzed during the current study will be made available by the corresponding author upon reasonable request.
